# The tooth movement efficiency of different orthodontic thermoplastics for clear aligners: study protocol for a randomized controlled clinical trial

**DOI:** 10.1186/s13063-023-07736-9

**Published:** 2023-10-23

**Keywords:** Orthodontic thermoplastics, Orthodontic tooth movement (OTM), Clear aligners, Randomized controlled trial

## Abstract

**Introduction:**

With regard to the esthetics and comfort of orthodontic treatment, the requirement for removable clear aligners (CAs) is increasing. Unlike conventional fixed orthodontic appliances, CAs were made of thermoplastic film by thermoforming on the personalized dental models. The construction of orthodontic thermoplastic is a critical factor for orthodontic tooth movement (OTM). Polyethylene terephthalate glycol-modified (PETG) and thermoplastic polyurethane (TPU) are the most commonly orthodontic thermoplastics; however, the evidence of the differences between different orthodontic thermoplastic are limited to vitro environment and the evidence in vivo environment is not available. Therefore, this trial aims to provide reliable evidence for orthodontists’ personalized treatment plans whether the two most commonly used orthodontic thermoplastics of PETG and TPU have differences in the efficiency of OTM.

**Methods and analysis:**

This randomized controlled clinical study will recruit 44 orthodontic patients for orthodontic treatment. All the subjects will be randomized into two groups (PETG and TPU, *n* = 22 for each group). In the first stage (M0 to M1), clear aligners will be made of two orthodontic thermoplastics and move the maxillary first or second premolars 2 mm. In the second stage, patients will take the standard orthodontic treatments. The primary outcome will be the efficiency of clear aligners made of different materials on the digital models. The secondary outcome will be the efficiency of clear aligners made of different materials on the cone-beam computed tomography (CBCT). The efficiency will be calculated through the superimposition of the digital models and CBCT.

**Discussion:**

The results from this trial will serve as evidence for orthodontists and manufacturers and clarify whether the difference in orthodontic thermoplastics significantly impacts the efficiency of OTM.

**Trial registration number:**

ChiCTR2300070980. Registered on 27 April 2023.

https://www.chictr.org.cn/showproj.html?proj=186253

## Introduction

Malocclusion can lead to negative psychological and social impacts on public health as one of the most common oral diseases [1]. Fixed appliances are the traditional treatment for malocclusion, but the requirement for personalized clear aligners made of orthodontic thermoplastics is increasing with regard to the esthetics and comfort of orthodontic treatment. The programmed movement with clear aligners provides a new method to measure increment and related factors of the orthodontic tooth movement (OTM). Several clinical researchers have studied the related factors using clear aligners. McGorray et al. [2] compared relaxin and a placebo using programmed aligners with regard to tooth movement and stability in a randomized clinical trial. They measured the movement weekly by digitized models and followed for four weeks to assess relapse. The treatment group has no differences in tooth movement in 8 and 12 weeks. Chisari et al. [3] examined the factors of age, sex, root length, bone levels, and bone quality on OTM by clear aligners. Digital models were measured for tooth movement, and cone-beam computed tomography was used to assess the bone and morphometric features. Their results show that the relationship between age and tooth movement is complex, and gender might have an influence. Nada et al. [4] studied 38 patients treated with Invisalign to compare the amount of tooth movement in predicted and achieved. The digital models were superimposed using Compare software, and the mean accuracy was 50%. The distal movement of the maxillary first premolar (57.1%) and the mesial movement of the maxillary second premolar (64.7%) were relatively accurate movements, respectively.

Apart from the clinical factors above, the construction and thickness of orthodontic thermoplastic materials are also related to the efficiency of clear aligners. Align Technology (San Jose, Calif)’s first marketed aligners were made from a single-layer rigid polyurethane and iteration by Exceed-30 and SmartTrack (a thermoplastic polyurethane, TPU) subsequently [5]. Another commonly orthodontic thermoplastics material of aligners manufactures is polyethylene terephthalate glycol-modified (PETG). Other orthodontic thermoplastic materials such as polypropylene (PP), polycarbonate (PC), and ethylene vinyl acetate (EVA) are also used [6]. The metals in fixed orthodontics have elastic properties. The deflection and tooth movement is predictable when forces are exerted by orthodontists [7, 8]. Orthodontic thermoplastic materials are viscoelastic and will occur stress relaxation in the oral cavity with intermittent loads [4, 9]. Therefore, the accurate assessment of the efficiency of aligners with different materials will increase the predictability of orthodontic treatment. Several studies have tested the aligners’ mechanical properties of different materials in vitro [10–12] environment. However, these studies are limited to observation time and vitro environment. Bollen et al. [13] compared two materials provided by Align Technology (hard and soft) and activation frequencies (1 and 2 weeks) on fifty-one subjects. They found that hard and soft aligners show no difference in the completion rate, and the frequency of 2 weeks has a higher completion rate. But the material constructions are not mentioned in their study. The tooth movement efficiency of different orthodontic thermoplastics still lacks clinical trial evidence.

Are there differences in the composition of different materials? This study will first provide reliable clinical evidence for orthodontists whether the two most commonly used orthodontic thermoplastics of PETG and TPU have differences in the efficiency of OTM. The efficiency of OTM will be evaluated by the movements of the teeth with programmed aligners.

## Methods and analysis

### Trial design

This study is a parallel-group, randomized controlled, double-blinded clinical trial (Fig. 1). The protocol is following the CONSORT guidelines (2010) [14]. This trial will recruit orthodontic patients from the Department of Orthodontics, Shanghai Stomatological Hospital. Clinical research coordinators will receive training on the design, methodology, clinical intervention, and keeping trial documentation of this study first. And then, they will explain the purpose and the arrangement of this study to the patients. The patients who are willing to participate in this study will be entered into the electronic data capture (EDC) system held on the computer server of Shanghai Stomatological Hospital.

**Fig. 1 Fig1:**
[figure not shown]
Flow chart of the trial design

Each participating patient will undergo the necessary medical examinations which include physical examinations, lateral cephalometry, cone beam computed tomography (CBCT), and intra-oral scan. The participants will be randomly divided into two equal groups (PETG and TPU)—at a ratio of 1:1. Different tests of two groups (PETG and TPU) will be recorded before the treatment (M0), 12 weeks after treatment (M1). The procedure shows in Fig. 2. This is a randomized clinical trial consisting of two parallel groups with equal randomization to detect the superiority of one intervention over the other in sagittal OTM of premolars.

**Fig. 2 Fig2:**
[figure not shown]
The critical nodes of this study

### Eligibility criteria

The patients will be assessed by orthodontists who have experience with clear aligners.

#### Inclusion criteria

The participants must meet the following criteria:Adult patients, aged 18–40 years.Permanent dentition, the first molar of the upper and lower and the anterior teeth are not missing.The crowding of dentition ≥ 5 mm, orthodontic treatment requires the extraction of the maxillary first premolar or the maxillary second premolar.Patients who are able to wear aligners as required time.

#### Exclusion criteria

The exclusion criteria of this study are as follows:Allergic to orthodontic thermoplastics.Patients need to have orthognathic (jaw) surgery.With symptoms or signs of temporomandibular joint disorders.With systemic diseases.

### Interventions

All participants’ maxillary first or second premolars will be selected at M0 to ensure that selected teeth can move towards the mesial or distal side 2 mm and not be blocked out by adjacent teeth. A series of 10 maxillary clear aligners were programmed to accomplish the movements from M0 to M1, and the increments of movement of the maxillary premolar will be designed as 0.2 mm in each step. The type of orthodontic thermoplastic for aligners manufactured depends on the card of their envelopes, PETG (Scheu, Iserlohn, Germany) or TPU (Maxflex, Taiwan). The clear aligners will be collected at the end of the fifth and tenth weeks. The patients will take an intra-oral scan at the same time. Routine follow-up will be conducted 2 weeks after programmed 10 steps.

The process and critical nodes of interventions in this study were showed in Fig. 2. The flow charts were printed and delivered to clinical doctors for reminders. In the first stage, from M0 to M1, the programmed movements were designed under the discussion of specialists.

Implementing use of PETG or TPU will not require alteration to usual care pathways, and the digital model registering, the aligners receiving, and the check of study number will continue for both trial arms.

### Patient and public involvement

The patients and the public will not be involved in the design, conduct, reporting, or dissemination plans in this trial.

### Outcome measures

The records of patients will be anonymized before analysis to eliminate analyst bias.

#### Primary outcome

The primary outcome will be the efficiency of clear aligners on OTM. Intra-oral scan (iTero, Align Technology, San Jose, Calif) will be collected in the key steps as shown in Fig. 2. The intra-scan digital models of different time points will be superimposed in the Rapidform2006 (INUS Technology Inc., Seoul, Korea) for measurements (Fig. 3). Landmarks’ three-dimensional coordinates in the buccal side (A1-A4, B1-B4) of the maxillary premolars will be recorded to calculate the crowns’ movements, including mesial tipping, distal tipping, buccal inclination, lingual inclination, rotation, intrusion, and extrusion.

**Fig. 3 Fig3:**
[figure not shown]
The measurements of OTM on digital models

#### Secondary outcomes

The CBCT images of different time points will be saved as Digital Imaging and Communications in Medicine (DICOM) format files and imported into Dolphin software (Dolphin Imaging & Management Solutions Corporation, Chatsworth, CA, USA) for superimposition based on voxel (Fig. 3.). The roots’ movements and the rotation angle will be inferred through the point marked (C_1_-C_4_, D_1_-D_2_). The lengths of the roots and crowns will also be measured (*h*_*1*_*, h*_*2*_) (Fig. 4). The efficiency will finally be calculated with the ratio of clinical tooth movements and designed movements. Correlations between age and OTM, as well as between gender and OTM, will be analyzed.

**Fig. 4 Fig4:**
[figure not shown]
The measurements of OTM on CBCT. The planned extracted tooth is surrounded by the green dotted line. The planned moved tooth is surrounded by the yellow dotted line. The target position of the moved tooth is surrounded by the red dotted line

### Target sample size

The sample size was calculated using PASS software (Utah, USA) and based on the primary outcome in this trial. The expectation hypothesis is that TPU orthodontic thermoplastics will increase the efficacy of orthodontic tooth movement (OTM). The studies of Chisari JR [3] and McGorray SP et al. [2] were used to estimate standard deviation. The standard deviation of OTM is 0.8 (TPU) and 0.616 (PETG) in their study. The sample size of 20 patients in a single group will achieve 80% power to detect a difference in 10 weeks with a 0.05 two-sided significance level. Considering a 10% dropout rate, this trial will recruit a total of 44 patients.

### Participant recruitment

Patients will be recruited at the orthodontic department in Shanghai Stomatological Hospital from 1 June 2023 to 31 December 2024 (anticipated). The notification will be published on the official website and hospital. The patients will be assessed by their orthodontists whether meet the inclusion criteria. The patients invited will have at least 2 weeks to make a decision.

### Sequence generation and randomization

Block randomization was used in this study. The subjects who met the criteria were randomly assigned to the experimental group and the control group according to the ratio of 1:1. A random allocation table was generated by an independent statistician through SAS 9.4 (SAS Institute Inc., Cary, NC, USA) software. Randomization allocation and masking were achieved by the envelope method.

### Participant allocation

In this study, patients’ allocation will be accomplished by numbered, opaque, sealed envelopes. The envelopes will be kept by the dental technician in charge of aligner manufacture. After the orthodontic design is confirmed, the dental technician will open the allocation envelope to identify the type of orthodontic thermoplastics. The allocation envelope will only be opened when clear aligners need to be manufactured.

### Blinding

This study is a double-blinded clinical trial (Fig. 5). The nurse collects the digital model registered with a study number and submits it to the dental technicians. The dental technicians will know and keep the group allocation when the corresponding envelope is open before manufacture. Then, unaware of the group allocation, the nurse receives the clear aligners with the study number. Because of the similar transparency and elasticity, clear aligners made of PETG and TPU are hard to distinguish. Thus, the orthodontists and patients only know the study number and are blinded for group allocation. The group allocation and patients’ information will be blinded to the analyst at the analyzing stage.

**Fig. 5 Fig5:**
[figure not shown]
The diagram of double-blinded design

### Data collection and management

#### Plans for data and records collected

The data will be recorded in case report forms (CRFs) designed by specialists and Zhejiang Taimei Technology Co., Ltd. The CRF will be filled out for each patient by coordinators. The fixed period of supervision will be taken by a qualified clinical research assistant. The clinical research assistant is blinded to the group allocation and reviews this trial’s informed consent and CRFs. The original CRFs will be saved in the data management center of Shanghai Stomatological Hospital.

### Data management

All patients’ image data, questionnaires, and measurements will be collected and checked regularly. The primary data will be coded to allow for the blinding of the analyst. The coded data will be exported into SPSS 24.0 (Chicago, the USA) for further analysis when the trial is accomplished.

### Post-trial care

All files of this trial will be retained for at least ten years at the end of the study.

### Confidentiality

All patients’ data will be securely stored with limited access. All participants will be informed that their records will have the possibility to be reviewed by the sponsor, the research ethics committee (EC), and the regulatory authority. All unpublished results and records will be deemed confidential. Any published reports will not contain personal data for the protection of personal privacy.

### *Statistical* methods

#### Statistical methods for outcomes

The primary and secondary outcomes are continuous variables. Descriptive statistics will be first used to summarize the outcomes of the study and show the distribution, mean differences, and standard deviations of the data. Spearman correlation was used to test for correlation between age/gender and the efficiency of OTM. The statistical analysis of the efficiency will be performed through the one-way ANOVA test. It will be considered significant when *P* < 0.05.

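### The primary efficiency comparison is fixed as an unadjusted one-way ANOVA, although tooth/direction, age and sex are known before allocation is revealed; adjusting for them is a cheap gain in precision

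*Protocol article*

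**What the plan says.** Under Statistical methods for outcomes, the protocol article fixes the test for efficiency: "The statistical analysis of the efficiency will be performed through the one-way ANOVA test". No covariate or stratum is named. Age and sex are handled apart from the treatment comparison: "Spearman correlation was used to test for correlation between age/gender and the efficiency of OTM". The Secondary outcomes section lists these correlations among its analyses.

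The treated tooth and direction vary between patients. Under Interventions, "maxillary first or second premolars will be selected at M0 to ensure that selected teeth can move towards the mesial or distal side 2 mm". Both are settled before the material is known, because under Participant allocation "After the orthodontic design is confirmed, the dental technician will open the allocation envelope". For the sequence, the article says "Block randomization was used in this study", at a 1:1 ratio, and names no stratification factor.

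The Introduction summarises earlier studies. On tooth and direction: "The distal movement of the maxillary first premolar (57.1%) and the mesial movement of the maxillary second premolar (64.7%) were relatively accurate movements". On age and sex, one cited study is reported to show that "the relationship between age and tooth movement is complex, and gender might have an influence". The next paragraph turns to material: "Apart from the clinical factors above, the construction and thickness of orthodontic thermoplastic materials are also related to the efficiency of clear aligners".

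**The concern.** A one-way ANOVA has a single factor, which here must be material. It therefore combines patients whose first premolar is moved with patients whose second premolar is moved, and it cannot use age or sex. The Introduction presents these as possible influences on movement, and the trial will hold all of them before allocation is revealed, so they are legitimate baseline covariates.

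Two things are at stake. Variance that the covariates explain stays in the error term and lowers power. With about 20 analysed patients per arm, a chance imbalance in one of them can also shift the observed material difference in the trial as realised. The Spearman correlations do not help with either. As described they take no account of arm, and for a two-level variable such as sex a rank coefficient does not give a male-female difference on the efficiency scale.

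**Working it through.** **Inputs from the protocol article.** SDs of 0.8 (TPU) and 0.616 (PETG), 20 per group, 80% power, two-sided 0.05 (Target sample size); designed movement 2 mm (Interventions); accuracies of 57.1% and 64.7% (Introduction).

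**Assumptions.** The SDs are in mm (no unit is given). Half the patients have each tooth/direction. R² for age and sex is not in the documents and is varied over a range.

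**1. The stated sample size.** No difference to detect is given, so 20 per group cannot be reproduced forward. Solving backwards:
- Common SD = √((0.8² + 0.616²)/2) = √0.5097 = 0.714 mm, or 0.714/2 = 36 percentage points of efficiency.
- Normal approximation: (1.960 + 0.842) × 0.714 × √(2/20) = 0.633 mm.
- t-test with 38 degrees of freedom: 0.649 mm, or 0.649/2 = about 32 percentage points.

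**2. Variance explained by tooth/direction.**
- Difference: 64.7 − 57.1 = 7.6 points; 0.076 × 2 mm = 0.152 mm.
- R² = 0.5 × 0.5 × 0.152² / 0.5097 = 0.0113, about 1%.

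**3. Chance imbalance in tooth/direction.** Under simple randomisation with 20 per arm:
- SD of the difference in proportions = √(2 × 0.25/20) = 0.158.
- Shift at 1 SD: 0.158 × 7.6 = 1.2 points (0.024 mm).
- Shift at 1.96 SD: 2.4 points (0.047 mm), which is 0.047/0.649 = about 7% of the detectable difference.

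**4. Power of the adjusted analysis at 0.649 mm.** The residual SD is 0.714 × √(1 − R²), with one degree of freedom lost per covariate. The noncentrality is 0.649 / (residual SD × √(2/20)).

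| Covariates | R² | Power |
|---|---|---|
| None (the plan) | – | 80.0% |
| Tooth/direction only | 1.1% (from the documents' figures) | 80.4% |
| Tooth, direction, age, sex | 0% (assumed) | 79.8% |
| same | 5% (assumed) | 81.7% |
| same | 10% (assumed) | 83.7% |
| same | 20% (assumed) | 87.7% |

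The last four rows charge 4 degrees of freedom. Coding tooth/direction as one two-level term uses 3 and changes power by no more than about 0.1 points.

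**5. The same on the scale of the detectable difference,** 0.649 × √(1 − R²), before lost degrees of freedom: 0.645 mm at 1.1%, 0.62 mm at 10% and 0.58 mm at 20%.

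**The case against.** The strongest objection is that nothing here is an error. With 1:1 randomisation, a one-way ANOVA on two arms is the equal-variance t-test. It estimates the material difference without bias, and its standard error already allows for chance imbalance. That stands: choosing a covariate-adjusted model is a choice of precision and does not repair an invalid test.

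A reader might infer that the protocol says these factors affect movement. It does not go so far. The age and sex wording is hedged and reports a cited study. For tooth and direction the article quotes two accuracies from a study of 38 patients, calls both relatively accurate, states no difference between them and gives no uncertainty. Tooth and direction are also fully confounded in that pair. This last matters little for the fix: the inclusion criteria require extraction of the first or second maxillary premolar, so the remaining one would usually move into the space, and one two-level term should capture most of it.

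A reader might also count the unnamed stratification as a fault. A journal article commonly leaves that detail to the full protocol, so it is context here and no finding.

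On Spearman, the correlations are listed as secondary analyses and were never offered as adjustment. The text does not say outright that arms are pooled; it only names no arm. For a two-level variable Spearman is a valid rank test. What remains is that it gives no male-female difference on the efficiency scale and, as described, ignores material.

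Finally, a straight-line age term fits poorly with a relation the Introduction calls complex. That is fair and bears on the form of the model.

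**Conclusion.** The point holds as a modest, inexpensive improvement. The protocol names a single-factor test that cannot use baseline variables which the trial will have and which its own Introduction treats as possibly relevant.

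The only gain that can be computed from the documents' figures is from tooth/direction: R² of about 1% and about 0.4 points of power, given a 50:50 mix, SDs in mm and the back-solved difference. The likely shift from imbalance, 1.2 points at 1 SD, is small beside a detectable difference of about 32 points. A gain of practical size, such as 83.7% power at R² = 10% or 87.7% at 20%, needs a contribution from age and sex that the documents neither give nor imply. It should not be quoted as expected.

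The stronger conclusion, that the planned comparison is biased or has the wrong type I error, is not supported. The case for adjusting is that the downside is about 0.2 points of power if the covariates explain nothing.

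**What to change.** Replace the one-way ANOVA with a pre-specified linear model of per-patient efficiency on material, tooth/direction (first premolar distal versus second premolar mesial, with any other combination given its own stated coding), age and sex. Report the adjusted material difference with its 95% CI as the primary result. Take the age association and the male-female difference in efficiency from the same model, in place of or beside the Spearman coefficients. State in advance how age enters, allowing a non-linear term if it is thought necessary. Fix all of this before unblinding.

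The cost is about 3 degrees of freedom out of 38, one more for each additional age or tooth/direction term. No new data are needed. Recruitment began on 1 June 2023, so this is a revision during the trial. By the protocol's own section on amendments it must be reported to the ethics committee and permitted; that section also speaks of revising and re-signing consent, so the committee should be asked whether an analysis-only change requires it.
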